### Hypotheses

The following hypotheses will be tested.

1 Patient stratified to the ‘high risk’ intervention based on the STarT Back tool will have better physical and psychological outcomes compared with their baseline scores and compared with the high risk historical control group.

2 Patients stratified to the ‘medium’ and ‘low risk’ groups based on the STarT Back tool will have significantly better physical and psychological outcomes compared with their baseline scores and equally good outcomes compared with the best-care historical control.

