### Analyses

All data will be entered into the IBM Statistical Package for the Social Sciences [39] and subsequently cleaned and checked for normality. Baseline differences between the treatment groups will be explored with independent t tests and chi square tests. Preliminary analysis will compare pre to post intervention outcomes for each treatment group to determine if a significant treatment effect is achieved by each of the stratified interventions using paired t-tests and Cohen’s d effect size statistics. The main analysis will compare treatment response between the stratified and control groups using analysis of covariance (ANCOVA) models with baseline measures as the covariate and treatment group as the between group factor. Statistical significance will be set at p < 0.05. Missing data will be imputed using the linear and logistic regression models applied by the multiple imputation functions in SPSS and an intention to treat analysis will be performed. We will also conduct a complete case analysis for those cases where we have complete follow up data. In the event of non normal data, non parametric tests will be performed instead. Exploratory economic analyses will be undertaken. Costs of each intervention will be calculated and quality-adjusted life years (QALYs) gained computed. These will be compared between interventions using independent t tests. Six month health care utilisation attendances and associated costs will be calculated for each patient and compared between the intervention groups using chi square tests for categorical data and t tests for continuous data.

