### Sample size and statistical power

The RMDQ has been chosen as the primary outcome measure in keeping with prior research. Although a change of 2.5 points on the RMDQ is considered to be a minimum clinically important difference [40], prior research has based sample calculations on a between group difference of 1.8 points [4]. As the high risk intervention is the new intervention, our first hypothesis will test the superiority of ‘stratified treatment’ over previous best care for the high risk subgroup. Following statistical review of both the original STarT Back trial [10] and existing data held by the researcher (RMDQ Sd_change_ = 4.7; correlation between pre and post RMDQ ρ = 0.592), sample size calculation was performed to detect an effect size of 0.38 for the new high risk intervention over controls, with 80% power and alpha (two-tailed) = 0.05. After adjusting for ANCOVA [41], the resulting minimum sample required for each of the historical and new high risk groups is 72 patients (n = 144).

Equivalence of the stratified treatment model to standard care for medium and low risk groups will be determined if the lower boundary of the 95% CI around the mean difference RMDQ does not exceed the 1.8 threshold. For this one sided 2.5% non-inferiority hypothesis, a minimum of 57 participants in each of the medium and low risk historical and new treatment groups is necessary (n = 228). Thus, the total minimum sample is 372 patients.

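### Hypothesis 2 is naturally read as claiming equally good physical and psychological outcomes, but only the RMDQ has a rule that can support such a claim

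*Protocol article*

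**What the plan says.** Three sections of the protocol article bear on this.

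- **Hypotheses.** The section says its hypotheses will be tested. Hypothesis 2 states that the medium- and low-risk groups will have "significantly better physical and psychological outcomes compared with their baseline scores and equally good outcomes compared with the best-care historical control".
- **Analyses.** One between-group method is given: "The main analysis will compare treatment response between the stratified and control groups using analysis of covariance (ANCOVA) models", with baseline as covariate. The decision rule is "Statistical significance will be set at p < 0.05". The section does not separate the superiority hypothesis (high risk) from the equally-good hypothesis (medium and low risk), and it does not separate the RMDQ from other outcomes.
- **Sample size and statistical power.** For the medium- and low-risk strata, the stratified model counts as equivalent to standard care when the "lower boundary of the 95% CI around the mean difference RMDQ does not exceed the 1.8 threshold". The section calls this a one-sided 2.5% non-inferiority hypothesis and sets at least 57 patients per group. The rule names the RMDQ and no other outcome.

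The RMDQ is the primary outcome and measures disability. Besides the RMDQ, the outcomes listed for the historical control are pain (VAS), distress (DRAM), back beliefs (BBQ), the Simmond's functional tests and lumbar flexibility.

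**The concern.** The hypothesis is broader than the rule that would decide it. On the natural reading, the outcomes said to be equally good are the physical and psychological outcomes named earlier in the same sentence. The margin rule covers one physical outcome, the RMDQ. No psychological outcome has a rule that could support the claim. What remains for those outcomes is a test of difference, which can show that the groups differ but cannot show that they do not.

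The low-risk stratum has most at stake. The control programme had four weekly classes of 1.5 hours followed by eight weeks of home exercise. Low-risk patients in the new model attend one 1.5-hour class and receive an exercise regime, a manual and a home log. Whether distress, beliefs or pain fare worse with less supervised contact is a real question there, and a statement that they were equally good would need evidence that rules out a meaningful deficit. In the medium-risk stratum the control sessions were much like the new ones, so the stakes are lower.

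**Working it through.** **Inputs.** From Sample size and statistical power: "RMDQ Sd_change_ = 4.7; correlation between pre and post RMDQ ρ = 0.592"; margin 1.8 points; effect size 0.38; 80% power and two-sided 5% for the high-risk comparison (72 per group); one-sided 2.5% and 57 per group for the medium- and low-risk comparisons. Power is not restated for non-inferiority, so 80% is assumed.

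**The plan's own figures.** ANCOVA factor: 1 − 0.592² = 0.6495.

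- High risk: a two-sample t calculation at effect size 0.38 gives 109.7 per group; 109.7 × 0.6495 = 71.2, so 72. This reproduces.
- Medium and low risk at one-sided 2.5%: 2 × [(1.960 + 0.842) × 4.7/1.8]² = 107.0, rounded up to 108 with the small-sample correction; 108 × 0.6495 = 70.1. Depending on rounding and on whether 0.38 or 1.8/4.7 is used, the answer is 70 to 72, not 57.
- At one-sided 5% the t calculation at 0.38 gives 86.3 × 0.6495 = 56.1, so 57.

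The 57 therefore matches one-sided 5% and not the stated 2.5%. That is a separate matter. Below, 57 is used because it is the stated minimum.

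**What a difference test can show on another outcome with 57 per group.** The article gives no pre-post correlation for the other scales, so ρ is taken from 0.592 (the RMDQ value) down to 0 (no gain from adjustment). Units are SDs of the outcome, with a normal approximation.

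- Standard error = √(2/57) × √(1 − ρ²). With ρ = 0.592: 0.1873 × 0.806 = 0.151. With ρ = 0: 0.187.
- 95% half-width = 1.96 × SE = 0.30 SD (ρ = 0.592) to 0.37 SD (ρ = 0).
- P(non-significant | true deficit d) = Φ(1.96 − d/SE) − Φ(−1.96 − d/SE).

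| True deficit | ρ = 0.592 | ρ = 0 |
|---|---|---|
| 0.2 SD | 74% | 81% |
| 0.3 SD | 49% | 64% |

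**If many more controls were available.** As a limit, take 57 new patients against an unlimited number of controls: SE = √(1/57) × √(1 − ρ²) = 0.107 to 0.132. The half-width is 0.21 to 0.26 SD. A 0.2 SD deficit is then non-significant 53 to 67% of the time, and a 0.3 SD deficit 20 to 38%.

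**The case against.** The strongest reply has four parts.

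1. **The article never says that non-significance will be taken as equality.** This stands. A reader might infer from the single p < 0.05 rule that it would be, but the document does not support that: the one place that says how equivalence is decided uses a confidence interval and a margin.
2. **The RMDQ is already properly covered.** This stands too. A reader might infer that the general p < 0.05 sentence also governs the medium- and low-risk RMDQ comparison. It does not: the sample size section names those strata, that outcome, the interval, the threshold and the one-sided 2.5% level, and a specific rule prevails over a general one. The ANCOVA is simply the model that can supply the interval.
3. **Margins for secondary outcomes are commonly left to an analysis plan that is not shown, and the equally-good clause does not itself repeat the words physical and psychological.** The first half stands as far as it goes: missing margins are no finding here, and none are requested. The second half is a possible reading but not the natural one. What remains is a mismatch between two things the article does state: a hypothesis to be tested on several outcomes, and an equivalence rule for one.
4. **The numbers rest on assumptions.** The RMDQ correlation need not hold for other scales, which is why a range is shown. Also, 57 is a minimum, and the controls come from what the article calls a large dataset. The unlimited-controls calculation answers this: the figures improve, but a 0.2 SD deficit would still be missed more often than not.

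**Conclusion.** The point holds for outcomes other than the RMDQ. Hypothesis 2, naturally read, claims equally good physical and psychological outcomes against the historical control in the medium- and low-risk strata, and the article offers nothing beyond a difference test to support that claim for any outcome except the RMDQ. The error rates shown make non-significance weak evidence at the planned minimum size.

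The sizes rest on 57 per group, a two-sided 5% test, and an assumed correlation between 0 and 0.592. The logical point does not depend on them. This is a matter of what the trial may conclude, not a flaw in the primary comparison.

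**What to change.** In Hypotheses, limit the equally-good clause of hypothesis 2 to the RMDQ, judged by the 95% interval against the 1.8-point margin already set under Sample size and statistical power. In Analyses, add that for all other outcomes in the medium- and low-risk strata the adjusted between-group difference will be reported with its 95% confidence interval, and that p ≥ 0.05 will not be interpreted as equally good.

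A cross-reference from Analyses to the RMDQ margin rule would help the reader but is optional, since that rule already applies.

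The change needs no more patients, data or analyses. Its cost is that the trial can no longer claim equality on secondary outcomes and can only report how large a deficit the data leave open.

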### Study design

This study is a non randomised controlled trial comparing a new stratified intervention to a historical control treatment, which is usual non-stratified care. The trial is thus pragmatic in nature and aims to establish the effectiveness of a treatment intervention in routine everyday practice [24]. The study will determine if the implementation of stratified care in a group setting, using the STarT Back risk stratification tool will result in significantly better physical and psychological outcomes in LBP patients, compared with historical control data collected between 2009–2011 [25]. Patient assessments will occur at baseline, at 12 weeks and 6 months following commencement of the treatment intervention. The primary endpoint for analysis is 6 months. Recruitment will take place between February 2012 and June 2013.

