This type of study design may be at risk of selection bias, but the choice of historical controls was made to allow comparability of interventions within a single clinical centre, thus removing the risk of differences in management between centres. Furthermore, since the new treatment paradigm necessitated a shift in management approach to include cognitive behavioural principles with subsequent staff training, the selection of historical controls averted any possible loss of fidelity of the routine care treatment which might have occurred if controls were recruited concurrently to the new intervention group. Other measures taken to minimise potential differences between the intervention and control treatments include; the control and historical interventions will be delivered to the same local population, referred from the same sources, using standard diagnostic and referral criteria. Both the historical and new interventions will be applied in the same clinical setting by therapists who will apply the pre and post treatment assessments in a standardised manner. The same end points will be chosen for the stratified treatment group as has been the practice for the historical controls and there will be no time lag between the historical data collection and the stratified intervention phase. This can be considered an appropriate design in the current study setting, where we have a large dataset documenting existing routine evaluation of clinical treatment outcomes [25]. Here the comparison of interest is between the existing standard management of LBP (the historical control group), in a single centre, to a new paradigm of care (intervention).

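### The normality fallback does not exempt the primary RMDQ comparison: it lets an unnamed non-parametric test replace the baseline-adjusted ANCOVA and leaves no confidence interval for the mean difference that the 1.8-point rule needs

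*Protocol article*

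**What the plan says.** All statements are in the protocol article.

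- **Analyses, main method.** Treatment response is compared between stratified and control groups by "analysis of covariance (ANCOVA) models with baseline measures as the covariate and treatment group as the between group factor".
- **Analyses, trigger and fallback.** The data are to be "subsequently cleaned and checked for normality"; model residuals are not mentioned. Later in the same section: "In the event of non normal data, non parametric tests will be performed instead". No test, estimator or threshold is given, and no outcome is excluded.
- **Sample size and statistical power, superiority.** The 72 per high-risk group is reached after an adjustment for ANCOVA, from an effect size of 0.38, 80% power, two-sided 5%, an SD of change of 4.7 and a pre-post correlation of 0.592.
- **Sample size and statistical power, non-inferiority.** For the medium- and low-risk groups the decision depends on whether the "lower boundary of the 95% CI around the mean difference RMDQ does not exceed the 1.8 threshold".
- **Study design.** The controls are historical and not randomised, and the authors grant that "This type of study design may be at risk of selection bias".

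**The concern.** The word for replacement in the fallback sentence is unqualified, so on its plain reading it reaches the ANCOVA. Three parts of the plan then stop fitting together.

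1. The usual rank test for two groups has no place for the baseline score, in a comparison where baseline differences cannot be assumed to be chance.
2. The high-risk sample size was reduced on the strength of the baseline covariate. A test without it is underpowered for the number recruited.
3. The non-inferiority rule is written in terms of a "95% CI around the mean difference RMDQ". A rank test yields a p-value and, at best, a shift estimate. It does not yield that interval.

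The trigger also looks at the wrong thing. ANCOVA makes its distributional assumption about residuals, and the RMDQ is a bounded, discrete score whose raw distribution can look non-normal while the adjusted comparison of means remains sound at 57 to 72 per arm.

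**Working it through.** **1. The plan's own figure.** For d = 0.38, two-sided 5% and 80% power, n = 2(1.96 + 0.8416)²/0.38² = 108.7, so 109 per group, or 110 with the t distribution. The ANCOVA factor is 1 − 0.592² = 0.6495. Then 109 × 0.6495 = 70.8 and 110 × 0.6495 = 71.4, which rounds up to 72. The stated 72 reproduces, and it depends on the covariate.

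**2. Power at 72 per group by the plan's own method (d = 0.38).**
- ANCOVA: 0.38/(√0.6495 × √(2/72)) = 2.83; power = Φ(2.83 − 1.96) = 0.81.
- Unadjusted t test: 0.38/√(2/72) = 2.28; power = Φ(0.32) = 0.63.
- Unadjusted Mann-Whitney, with relative efficiency 3/π = 0.955 under normality: power 0.61. It would need 109/0.955, about 115 per group.

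**3. Power on the RMDQ scale.** The SD of change and the correlation imply an SD of each score of 4.7/√(2(1 − 0.592)) = 5.20, and a residual SD of 5.20 × √0.6495 = 4.19. For a 1.8-point effect and 72 per group (√(2/72) = 1/6):

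| Analysis | SD used | Power |
|---|---|---|
| ANCOVA | 4.19 | 0.73 |
| Mann-Whitney, change scores | 4.7/√0.955 | 0.61 |
| Mann-Whitney, follow-up scores | 5.20/√0.955 | 0.53 |

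Simulations with normal data agree to within about 3 percentage points. ANCOVA has 73% here and 81% in step 2 because 0.38 matches 1.8/4.7, an effect scaled by the SD of change, to which the ANCOVA factor was then applied. That is a separate matter; the contrast between methods appears on both scales.

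**4. Bias with no treatment effect.** The documents give no baseline imbalance; 1 and 2 points are assumed. Suppose first that both groups regress to a common mean, so a baseline gap δ leaves a follow-up gap of 0.592δ and a change gap of (0.592 − 1)δ = −0.408δ.

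| Analysis | Bias, δ = 1 | Bias, δ = 2 | False positives, δ = 1 | False positives, δ = 2 |
|---|---|---|---|---|
| ANCOVA | 0 | 0 | about 5% | about 5% |
| Mann-Whitney, follow-up | 0.59 | 1.18 | 9–10% | 25–27% |
| Mann-Whitney, change | −0.41 | −0.82 | 7–9% | 17–19% |

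The percentages are ranges over simulations of 2,000 to 4,000 trials per scenario. On follow-up scores, a 2-point imbalance uses 1.18/1.8 = 66% of the margin.

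Now suppose that, without any effect, the whole gap persists. The ANCOVA bias is δ − 0.592δ = 0.408δ, and its false-positive rate is about 8% and 21%. Mann-Whitney on change scores stays near 5%. Mann-Whitney on follow-up scores carries the full 1 or 2 points as bias.

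**5. The non-inferiority rule.** The rule needs an interval for a mean difference in RMDQ points. Mann-Whitney gives none. Its companion Hodges-Lehmann interval is in RMDQ points, but it describes an unadjusted location shift. A rank ANCOVA such as Quade's works on ranks and gives no RMDQ-point interval. If the Hodges-Lehmann interval on follow-up scores were used at 57 per arm, with the true difference exactly at the margin, common-mean regression and an imbalance of 1 or 2 points favouring the new arm, non-inferiority would be wrongly declared in about 8% or 21% of trials against a nominal 2.5%. ANCOVA stays at about 2%.

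**The case against.** **The test is unnamed.** The article says only that non-parametric tests will be used. Rank ANCOVA is one, and it keeps the baseline score: in the setting of step 3, Quade's test has about 70% power, and its error rate is about 5% at both imbalances under common-mean regression. This stands. A reader might infer that the fallback necessarily discards baseline adjustment; the text does not go that far. It permits the loss and does nothing to prevent it. The missing interval for the mean difference does not depend on which rank method is chosen.

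**The power loss is computed for normal data, while the rule acts only on non-normal data.** This also stands. With strongly skewed (lognormal) residuals and a 1.8-point shift, power is about 78% for ANCOVA, 74% and 91% for Mann-Whitney on follow-up and change scores, and 97% for rank ANCOVA. The loss can shrink or reverse. The figures in steps 2 and 3 show the cost of losing the covariate, not a forecast for this trial.

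**ANCOVA is not a guarantee in a non-randomised comparison.** Correct, as step 4 shows for a persisting gap.

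**Other safeguards exist.** A reader might think baseline adjustment is the study's only protection. The Aims call the control matched, comparisons are made within STarT Back risk strata, and the Study design section lists a common population, common referral sources and standardised assessment. That stronger reading fails.

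**The specific non-inferiority rule may override a general sentence about tests.** Possibly, but nothing says so. The plan could then hold a rank p-value and a parametric interval for the same outcome without stating which decides.

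**Costs.** One might extend the fallback to skewed costs. The economic comparisons are described after the fallback sentence, as exploratory, with their own t tests, so the article does not support that extension.

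**Conclusion.** The point holds in a limited form. As written, the fallback can replace the primary baseline-adjusted RMDQ analysis, and it leaves the 1.8-point decision without the interval that the sample size section prescribes. The second consequence follows whichever rank method is used. The first depends on the choice of test and is real for Mann-Whitney.

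For Mann-Whitney at 72 per arm under normality, power falls from about 73% to about 53% or 60%. False-positive rates on follow-up scores rise to about 9% or 25% under an assumed imbalance of 1 or 2 points with regression to a common mean. These are conditional illustrations: the imbalance is not in the documents, skewed data can reverse the power ranking, and a persisting group gap removes ANCOVA's advantage over change scores. The article gives no RMDQ distribution, so how likely the rule is to trigger cannot be stated either. The wording should be corrected, since the contradiction lies within the plan and is easily removed.

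**What to change.** Replace the fallback sentence, for the RMDQ, with a rule along these lines:

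- The baseline-adjusted ANCOVA is the primary analysis irrespective of the normality check.
- Model assumptions are judged on residuals, not raw scores.
- The adjusted mean difference is reported with a bootstrap or heteroscedasticity-robust 95% confidence interval, and that interval serves both the superiority decision (high risk) and the non-inferiority decision (medium and low risk).
- Rank-based methods are sensitivity analyses. They should be named in advance, and one that keeps the baseline score, such as Quade's rank ANCOVA, is preferable to an unadjusted Mann-Whitney test.

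Because ANCOVA itself depends on how a baseline gap would evolve without treatment, a change-score analysis is a useful further sensitivity check.

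The cost is a few sentences of wording and a robust or bootstrap option in the analysis. No patients, visits or data are added. The one trade-off is some power compared with a rank method if residuals turn out strongly skewed, and the sensitivity analysis would show that. The change should be recorded before the six-month outcomes are analysed.

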## Abstract

**Background:**

Low back pain (LBP) is costly to society and improving patient outcomes is a priority. Stratifying LBP patients into more homogenous groups is advocated to improve patient outcome. The STarT Back tool, a prognostic screening tool has demonstrated efficacy and greater cost effectiveness in physiotherapy settings. The management of LBP patients in groups is common but to date the utility of the STarT Back tool in group settings has not been explored. The aim of this study is to determine if the implementation of ‘stratified care’ when delivered in a group setting will lead to significantly better physical and psychological outcomes and greater cost effectiveness in LBP patients compared to a bestcare historical control group.

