**Methods/Design:**

This study is a non randomised controlled trial. Low back pain patients recruited from the Waterford Primary Care area (population = 47,000) will be stratified into low, medium or high risk of persisting symptoms using the STarT Back Tool. Low risk patients will be offered a single one off education/exercise class offering positive messages on LBP management in line with recommended guidelines. Medium risk patients will be offered a 12 week group exercise/education intervention addressing their dominant physical obstacles to recovery. A 12 week group cognitive behavioural approach will be delivered to the high risk patients, characterised by the presence of high levels of psychosocial prognostic factors. These patients will be compared with a historical control group where therapists were blinded as to the risk stratification of patients and a generic group intervention was delivered to all patients, irrespective of their initial risk stratification. The primary outcome measure will be disability (Roland Morris Disability Questionnaire). Secondary outcomes will include back pain intensity (Visual Analogue Scale), distress (Distress and Risk Assessment Method), back beliefs (Back Beliefs Questionnaire), health status (Euroqol), global benefit (7 point likert scale), satisfaction (7 point likert scale), cost effectiveness and functional status. Outcome will be measured at baseline, 12 weeks and 6 months.

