## Methods/Design

### Aims

The main objective of this study is to determine if the implementation of ‘stratified care’ when delivered in a group setting will lead to significantly better physical and psychological outcomes in a group of patients with non specific LBP, compared to a matched best care historical control. The historical control group will consist of individuals who attended the Back Pain Clinic between 2008 and 2011. Evaluation of treatment effect will be made within each of the stratified treatment groups and comparisons will be made between the stratified group outcomes and best care historical control. Secondary analysis will compare the delivery costs of the historical and stratified interventions.

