#### Outcome measures

The outcome measures assess the domains of disability, pain, psychosocial and health status, global perceived benefit, satisfaction and functional status (Table 2). The primary outcome measure will evaluate change in functional disability due to LBP measured by the Roland Morris Disability Questionnaire (RMDQ). The RMDQ is widely used in LBP studies in Primary Care and has demonstrated good validity, reliability and responsiveness [31]. All outcome measures demonstrate proven validity and reliability in their particular domain - pain (VAS 0–10) [32], anxiety and depression (DRAM) [33], back beliefs (BBQ) [34], global perceived benefit scale and satisfaction scale (seven point likert scale) [37]. Functional outcomes include sit to stand test, functional reach test and 50 ft. walk test [35] and lumbar spine flexion range of motion [36].

With respect to cost analysis, each patient will be asked to complete a cost diary documenting their medication costs and health care costs (direct costs) for a retrospective three months, prior to attending the clinic and for the prospective six months while participating in the study. The health economic evaluation will consist of a cost benefit analysis and a cost utility analysis, with utility measured by the EuroQol (EQ-5D) [38]. The cost of each treatment strategy will be determined prospectively and includes staff time, overheads and equipment.

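### The economic analysis is specified as separate significance tests on costs and on QALYs, which give no uncertainty for cost effectiveness and no basis for weighing extra cost against gain

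*Protocol article*

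**What the plan says.** The abstract's Background makes "greater cost effectiveness in LBP patients compared to a bestcare historical control group" part of the aim, and its Methods/Design paragraph includes "cost effectiveness and functional status" among the secondary outcomes. Under Outcome measures the article states: "The health economic evaluation will consist of a cost benefit analysis and a cost utility analysis", with EQ-5D as the utility measure. The Conclusions again present cost effectiveness as something the study will investigate.

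The Analyses section then sets out what will be done. It opens with "Exploratory economic analyses will be undertaken" and continues with "Costs of each intervention will be calculated and quality-adjusted life years (QALYs) gained computed", followed by "These will be compared between interventions using independent t tests". Six-month attendances and their costs are compared by "chi square tests for categorical data and t tests for continuous data". The Aims section is narrower than all of these: "Secondary analysis will compare the delivery costs of the historical and stratified interventions".

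**The concern.** Cost effectiveness is a relation between a cost difference and an effect difference. The only inference that the article specifies treats the two apart. If a strategy costs more and may do more good, one p-value for cost and another for QALYs do not say whether the gain is worth the cost, or how sure one can be. Two non-significant results are easily read as no economic difference, and a significant cost with a non-significant QALY gain as poor value. Neither reading follows.

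Two further points arise. A cost-benefit analysis values health benefit in money, and the article describes no such valuation. Delivery cost per patient is set mainly by session length and class size, so a significance test on it says little that the timetable does not already say.

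At stake is the economic conclusion only. The hypotheses, the sample size and the primary disability comparison do not depend on it.

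**Working it through.** The article gives no cost or QALY means, SDs or threshold, so there is no figure to reproduce. The check has three parts.

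**1. Promise against method.**

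- Cost-utility analysis: costs and QALYs are computed and each is tested. The two mean differences would give a point ratio. No interval, net benefit or threshold is stated.
- Cost-benefit analysis: cost diaries record medication and health care costs. No money value is placed on health gain.
- Delivery costs (Aims): calculated for each intervention, then tested.

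**2. Where a trade-off arises by design.** Class hours and class sizes come from the sections describing the interventions. One therapist per class is an assumption. Staff hours per patient = class hours / class size.

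- High risk: 4 × 2 h = 8 h over 4 to 6 patients, so 8/6 to 8/4 = 1.33 to 2.0.
- Historical control: 4 × 1.5 h = 6 h over 6 to 10 patients, so 6/10 to 6/6 = 0.6 to 1.0.
- Medium risk: 4 × 1.5 h = 6 h over 6 to 10 patients, so 0.6 to 1.0, the same as the control.
- Low risk: 1.5 h over 3 to 5 patients, so 1.5/5 to 1.5/3 = 0.3 to 0.5.

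The high-risk and control ranges do not overlap (1.33 is above 1.0), nor do the low-risk and control ranges (0.5 is below 0.6). If delivery cost is assigned to patients in this way, a t test on it will reject at any realistic sample size, whatever happens to the patients. If all class sizes in each range are equally common, high-risk care averages 24 h over 15 patients = 1.60 h and control 30 h over 40 patients = 0.75 h, a difference of 0.85 h.

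**3. What separate tests miss (illustration; every economic input is assumed).** Take the planned 72 high-risk patients per group. The SE of a mean difference is SD × √(2/72) = SD/6. Assume a cost difference of +60 euro (SD 400) and a QALY difference of +0.02 (SD 0.10), and use normal approximations.

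- Cost: SE = 400/6 = 66.7; z = 60/66.7 = 0.90; p = 0.37.
- QALY: SE = 0.10/6 = 0.0167; z = 0.02/0.0167 = 1.20; p = 0.23.
- Point cost per QALY: 60/0.02 = 3,000 euro.
- Net benefit at an assumed 20,000 euro per QALY: 20,000 × 0.02 − 60 = 340 euro. With uncorrelated cost and QALY, SE = √((20,000 × 0.0167)² + 66.7²) = √(333.3² + 66.7²) = 339.9. The probability that net benefit is positive is Φ(340/339.9) = 0.84, and the 95% interval is 340 ± 1.96 × 339.9, or −326 to 1,006 euro.
- Over correlations of −0.5 to 0.5 and thresholds of 20,000 to 45,000 euro, that probability runs from 0.82 to 0.88.

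The two tests would be reported as no difference twice. The joint analysis shows evidence that leans towards the intervention but is not conclusive. The first two steps and the point ratio are available from the stated plan; the last two are not.

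**The case against.** The strongest reply is that the article names a cost-utility analysis, which by definition relates cost to QALYs, and that a condensed article may leave thresholds and bootstrap details to a fuller document. This stands in part. A reader might infer that costs and QALYs will never be combined and that no cost-utility result can come out. The documents do not support that: the analysis is named, and the planned mean differences give a point ratio or show dominance. But the article is not merely silent on inference. It states its method, and that method does not answer the question posed.

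The exploratory label is also a fair point. It lowers the weight of the matter but does not make separate tests suitable, since the abstract and the Conclusions carry cost effectiveness without that label.

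A reader might also infer that every stratum involves a delivery trade-off. It does not: medium-risk care has the same class format as the control, and low-risk care that is cheaper with equal outcome would involve none.

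On the cost-benefit part, averted health care cost is a monetary benefit and the diaries would capture it. That is a narrow benefit, however, and leaves health gain unvalued.

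Finally, the article does not say at what level delivery cost is calculated, so the remark about testing it depends on costs being assigned per patient.

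**Conclusion.** The point holds in a limited form. The stated economic inference consists of separate tests, and these do not supply the uncertainty or the weighing of cost against effect that the promised results need. The gap matters most for high-risk care, where staff time per patient is higher by design: 1.33 to 2.0 h against 0.6 to 1.0 h, with one therapist per class assumed. The sign of the total cost difference is unknown, because overheads, equipment and six-month health care use also count. The cost-benefit label has no described valuation of health benefit behind it.

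The euro-per-QALY and probability figures show only how separate and joint analyses can differ. They rest on assumed inputs and predict nothing about this trial.

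One condition limits the remedy. The section on the historical control lists neither EQ-5D nor cost diaries for those patients and mentions assessment only at baseline and 12 weeks. The recruitment section says that they completed the same self-report questionnaires as the intervention group. A reader might infer that six-month control QALYs and costs do not exist; the article leaves this unclear and does not settle it.

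**What to change.** In the Analyses section, replace the separate economic tests with the following.

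- Within each risk stratum, estimate incremental cost (delivery plus health care use) and incremental QALYs jointly. Report cost per QALY and incremental net monetary benefit over stated thresholds, with bootstrap intervals that keep each patient's cost and QALY paired.
- Report delivery cost per patient as a calculated figure over the class-size range, without a significance test.
- Rename the cost-benefit analysis as a net-benefit analysis.

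Before adopting this, state whether the historical controls have EQ-5D and cost data over the same period as the intervention patients. If they do not, limit the economic conclusion to the delivery-cost comparison in the Aims and drop the cost-effectiveness claim from the abstract and the Conclusions.

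The cost is one rewritten paragraph and a modest amount of extra analysis. No further data are needed from intervention patients. For the controls, the joint analysis is possible only if the data already exist.
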